***Methods and procedures***

Design: A multicentre, randomized, controlled phase III study will be conducted in 3 study sites in Sweden (Stockholm, Gothenburg and Umeå).

Study design and protocol will follow the CONSORT standards and are in accordance with the principles of the Declaration of Helsinki and Good Clinical Practice. The study protocol will be approved by the ethical committee in Stockholm and will be submitted for publication on *clinicaltrials.gov.*

Study Endpoints

The primary aim of the study is to compare the effectiveness of a) intensive training with HAL, b) intensive training without HAL and c) standard training, in a later phase (1-10 years) after stroke on independence in ambulation after intervention by comparing the Functional Ambulation Category in each group.

Secondary aims comprise the effectiveness of training with HAL on independence gait function and quality, cardiovascular function, activity of daily living and participation assessed at the end of intervention and at a 6 and 12 months follow-up. Effects on health care consumption during 12 months after the intervention will be explored and treatment related adverse events during the study will be documented. Further, associations between range of movement, strength and spasticity versus HAL mediated recovery will also be explored.

Setting: Setting: The study will be performed simultaneously at Danderyd University Hospital and Department of Clinical Sciences, Karolinska Institutet in Stockholm; Sahlgrenska University Hospital and University of Gothenburg in Gothenburg; Norrland University Hospital and Umeå University in Umeå.

*Recruitment of patients*

Eligible are persons, aged 18-70 years, recruited from out-patient rehabilitation units where they have passed a regular rehabilitation program due to stroke related hemiparesis/central paresis of the lower extremity (LE) after an ischemic or haemorrhagic first ever stroke (assessed by a stroke physician and verified by CT or MRI examination- this data will be collected from initial referral to the unit or in case of missing data, by contacting the physician or the medical records after approval by the study participant).

Inclusion criteria: 1-10 years since stroke onset; able to walk but not independently, i.e. need of manual support or close supervision due to lower extremity paresis, FAC score 2-3 or FAC 4 combined with gait speed <0.8m/s according to 10 meter walk test, which corresponds to limitations in community ambulation (Bowden et al 2008); ability to understand training instructions as well as written and oral study information and to express informed consent or by proxy; body size compatible with the HAL suit.

Exclusion criteria: contracture restricting gait movements at any lower limb joint; cardiovascular or other somatic condition incompatible with intensive gait training; severe, contagious infections (e.g. Methicillin Resistant Staphylococcus Aureus (MRSA) or Extended Spectrum Beta Lactamase bacteria).

*Randomisation*

Randomisation will be performed by a clinician, who is not otherwise involved in the study according to a block design procedure where patients are randomized into each group.

*Interventions*

To standardize the training procedure, training with HAL is performed on a treadmill and to enable body weight support. Body weight support is used to prevent falls and to unburden the weight of the suit (9 kg). The training program is performed by physiotherapists, trained in the HAL method and the study procedures.

The conventional gait training is performed according to current best evidence based practice and may include over ground walking with assistance and/or assistant devices as well as the use of a treadmill and body weight support and training of gait function in activities of daily living

Intensive gait training with HAL is performed 1 session/day, 3 days/week for 6 weeks and each session will not exceed 60 min of effective walking time with HAL. In addition, each session will include conventional gait training that will not exceed 30 min effective training time. At the end of the 6 weeks, the physiotherapist that has been engaged in the patient’s conventional training will perform 1-2 home visits to inform/educate the patient and those who are providing assistance to the patient in how the patient can make use of any gains in gait function during activities of daily living. The 1^st^ control group will receive conventional gait training performed 1 session/day, 3 days/week for 6 weeks that will not exceed 1h 30 min effective training time. The 2nd control group will not receive an intervention.

*Data collection*

All data collection will follow and be documented in individual Case Report Forms (CRF).

The HAL-training in Study I and II will documented in a standardized protocol, developed and tested in previous and ongoing studies. Conventional gait training in Study I will be documented based on data collected from medical records at the rehabilitation units.

Intensive gait training with and without HAL in Study II will be documented according to preformed forms. The participants in the 2d control group in who are not receiving an intervention, will document any scheduled training sessions in an web based application (app) or will be interviewed once a week according to a standardized protocol.

*Assessments*

Assessments will be made with valid instruments (not referenced in detail here) and performed once at baseline, immediately after the intervention period and at 6 and 12 months after the intervention period by a senior physician specialist physician, and by a blinded, experienced physiotherapist. The time points for the assessments are presented in the Table.

*Screening of function and disability:*

Data on Stroke type and localization will be collected from the medical records at the study sites. Body function will be assessed by use of the NIH Stroke Scale (NIHSS), mental function with Montreal Cognitive Assessment, executive function with the questionnaire Dysexecutive Questionnaire included in BADS (Behavioural Assessment of the Dysexecutive Syndrome), anxiety and depression with the Hospital Anxiety and Depression Scale and activity and participation by means of the Barthel Index and Modified Rankin Scale.

*Primary outcome measure*

The primary outcome will be the Functional Ambulation Categories (Holden 1984) that assesses activity in terms of independence in walking.

*Secondary outcome measures:*

Body function in terms of sensory function, pain and control of voluntary movement will be assessed with the Fugl Meyer Scale (FM-LE) and spasticity in the lower extremities with the Modified Ashworth Scale and the neuroflexor module and range of movement with the goniometer. Gait pattern function and walking will be assessed in laboratory gait analyses.

Activities and Participation in terms of walking will be tested with the 10 meter walk test, 2 and 6 minutes’ walk test combined with the Borg RPE scale for endurance, the accelerometer SenseWear Pro2 will be used to assess energy expenditure and physical activity (number of steps) in everyday life balance in activity with the Berg Balance Scale, and perceived functioning and disability with the Stroke Impact Scale (SIS).

Qualitative evaluation based on interviews will be performed in subgroups. Treatment related adverse events will be documented.

Data on registered health care and rehabilitation utilization during 12 months after the intervention period will be retrieved from the local County Councils at the study sites.

*Other assessments*

Resistance to passive stretch of lower leg muscles (spasticity) by use of new Neuroflexor/foot module - for exploratory analyses of prediction.

HbA1c (long- term blood glucose level), plasma lipid profile, Blood pressure (over day curve); oxygen uptake for assessment of energy expenditure (performed in subgroup only); Body Mass Index; drug use – pharmacological, including antidepressants, smoking and alcohol will be documented.

*Power calculation and statistics*

Power calculation is based on previous studies of motor function after stroke and of the effects of training with HAL. Using FAC as the primary outcome measure and the expected minimum difference of one category between treatment groups, a significance level of 5% and a power of 80%, and an expected minimal loss of patients per treatment arm,

The study will require 54 (18x3) patients at each study sight, i.e. 162 patients in total.

Populations to be used for statistical analyses:

(1) All Available-Patients (AAP) population - all randomised patients regardless of further participation will be used to present demographic and baseline characteristics.

(2) Intent-to-Treat (ITT) population - all patients, who were randomised and started the intervention program regardless if and when they withdrew, will be used to present all efficacy and safety data.

Hypothesis testing will be carried out at the 5% (two-sided) significance level, descriptive summary statistics presented for continuous variables (median, minimum and maximum, arithmetic mean, 95% confidence intervals (CI), standard deviation (SD), standard error).

In non-parametric analyses, the minimum, maximum, median, 5th, 25th, 75th, and 95th percentiles will be calculated. The median difference between treatment groups and the corresponding 95% CI will be presented as statistical analysis outputs. For categorical variables, counts and percentages will be presented, and comparison of intervention groups by use of generalised linear models to provide odds ratios (ORs), corresponding 95% CI and p-values< 0.05. For secondary endpoints we will use mixed models to explore change between and within groups over time.

Adverse events during the study period adverse events (such as falls, skin impact, pain during training session with HAL; new stroke or other cardiovascular events etc.)

will be documented according to a preformed protocol and their association or not to the Interventions will be classified by an external partner. Prevention of these will be standardised over study sites.

*Recruitment period*

Inclusion of patients will be ongoing from September 2015 – October 2017 with follow ups completed in November 2018.

*Limitations, potential bias*

Patients will be recruited from out-patient clinics which enables a recruitment of patients that have been assessed and found to be in need of rehabilitation interventions in the long-term phase after stroke. By using this procedure we will not be able to recruit patients who have not received rehabilitation interventions in out-patient care However, given the access to out-patient rehabilitation units in Stockholm we consider the risk of missing patients who meets the inclusion exclusion critera to be small. Thus, the study samples will represent those with needs of and probably with the greatest potential benefits from improved rehabilitation interventions. Based on our prior experiences, there might be a risk for an uneven gender distribution with more male than female. The reason for this is not clear but women tend to suffer a stroke later in life compared to men. Efforts will be made to avoid a bias in this respect.

*Generalisability*

Regarding the multicentre design, recruitment process and sample size, we expect the findings to be generalisable to the stroke population at focus (see limitiations)

*Funding*

Ongoing exploratory studies are supported by grants. The current project is investigator/academically initiated and driven but with substantial support (See Budget&Resources) from Cyberdyne Inc providing HAL equipment and technical support. The project is otherwise dependent on grants for clinical research as well as contributions from the academic expertise invlolved. Cyberdyne Inc or any other person or body with a financial interest in HAL will not participate in the planning, performance of reporting of the studies. Unlike trials of new pharmacological drugs, there is not tradition or practice for full support from medico technical companies phase III studies of new products, although modern medicine requires similar evidence for technical treatment devices.

Each study site will apply for additional funding as needed (substudies).

*Time plan*

December 2014- September 2015: Coordination of study sites and teams including course for management of the HAL system and standardised performance of assessments and data collection. Submission of study protocols for publication on ClinicalTrials.gov.

September 2015 – October 2017: Inclusion of study participants.

November 2018: Follow up ends.

October 2016 – November 2018: collection of health care utilisation data.

2018-2019 data analyses and reports in relevant international, scientific journals on subsets of data will continue.

*Organisation, study groups, study members/roles, organisations*

This project is based on a consortium for studies of HAL applications in Sweden and Japan (see further below). The groups in Stockholm, Gothenburg and Umeå have collaborated in related areas since long. The group in Umeå represents excellence in research on human motor disorders.

Stockholm: The clinical research group is based on the Department of Rehabilitation Medicine, Danderyd University Hospital (RMD) and members are affiliated to Karolinska Institutet. The group has a main focus on motor disorders after stroke and participates in several projects related to the development, evaluation and implementation of new technology for clinical diagnostics, training and everyday support in neurorehabilitation. The group has an extensive, international network for collaboration and is one partner in projects supported by grants from Vinnova, EU, biotech companies, Promobilia, the Swedish Stroke Association and others.

[name], professor, will serve as chief investigator.

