**New technology for individualised, intensive training of gait after stroke– phase III trials**

**Study II**

**Purpose and aims**

The overall purpose of this project is to establish the added value of training with the Hybrid Assistive Limb (HAL) exoskeleton system as part of regular rehabilitation intervention programs after stroke.

The main specific aims are

1. to demonstrate the effect of intensive training with HAL in comparison with intensive training without HAL and with standard care only, in a later phase (1-10 years) after stroke with regard to gait and cardio-vascular function, activity and participation;
2. to estimate health care utilisation and cost effectiveness of using the HAL during the first year after stroke.

**
[figure not shown]
**

Figure 1. Illustratíon of HAL exoskeleton for gait training on treadmill with Body Weight Support.

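### As written, home education visits go only to the HAL arm and are not ordered against the post-intervention FAC, so the HAL versus no-HAL contrast includes a non-HAL co-intervention, mainly in the 6- and 12-month daily-life outcomes

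*Protocol*

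**What the plan says.** Under Purpose and aims, the Protocol sets out "to demonstrate the effect of intensive training with HAL in comparison with intensive training without HAL and with standard care only". Study Endpoints (Methods and procedures) repeats the comparison as "a) intensive training with HAL, b) intensive training without HAL and c) standard training", with FAC after the intervention as the primary outcome.

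The Interventions text describes the arms one after another. The HAL arm has up to 60 minutes of HAL walking per session. It continues: "In addition, each session will include conventional gait training that will not exceed 30 min effective training time". Next comes the home-visit sentence: when the six weeks finish, the physiotherapist from the patient's conventional training "will perform 1-2 home visits to inform/educate the patient and those who are providing assistance to the patient". The stated subject of the visits is "how the patient can make use of any gains in gait function during activities of daily living".

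The text then turns to the first control group, which "will receive conventional gait training performed 1 session/day, 3 days/week for 6 weeks that will not exceed 1h 30 min effective training time". No visit is named for that group there or elsewhere in the visible text. The second control group receives no intervention.

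The Assessments text places the first follow-up assessment directly after the intervention period, then at 6 and 12 months, and refers to a table of time points that is not reproduced in the copy reviewed. Study Endpoints lists among the secondary aims "activity of daily living and participation assessed at the end of intervention and at a 6 and 12 months follow-up".

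**The concern.** The comparison of the two training arms is meant to show what HAL adds to intensive training, and session time has been matched for that purpose. A site that follows the text would also give one of these arms home education for the patient and helpers, and give the other arm none. Within these two arms, visits and allocation coincide completely, so no analysis can separate the effect of the visits from the effect of training with HAL. Blinding the assessing physiotherapist does not help, because the difference lies in the treatment received.

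The visits aim to carry gait gains into daily life, and several secondary outcomes measure daily life: everyday step counts, the Stroke Impact Scale and 12-month health care use. If the visits also precede the post-intervention assessment, the primary FAC is exposed too. Who receives which intervention, and when, is protocol content and cannot be left to an analysis plan.

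**Working it through.** **Inputs.** Power calculation and statistics: 18 patients per arm per site, three arms, three sites, 162 in total. Interventions: 3 sessions a week for 6 weeks; ceilings of 60 + 30 minutes (HAL arm) and 90 minutes (first control group); 1 to 2 visits (HAL arm).

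**Plan's own figure.** 18 × 3 = 54 per site and 54 × 3 = 162, as stated. Per arm: 162 / 3 = 54.

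**Is training time matched?** Sessions: 3 × 6 = 18 in each training arm. Ceiling per session: 60 + 30 = 90 minutes against 90 minutes. Ceiling over the programme: 18 × 90 = 1,620 minutes = 27 h in both arms. The visits are therefore additional to a matched training allowance.

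**How much is added?**

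| Quantity | HAL arm | First control group |
|---|---|---|
| Visits, whole arm | 54 × 1 = 54 to 54 × 2 = 108 | none named |
| Visits per site | 18 × 1 = 18 to 18 × 2 = 36 | none named |
| Scheduled contacts per patient | 18 + 1 = 19 to 18 + 2 = 20 | 18 |

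The excess in contacts is 1/18 = 5.6% to 2/18 = 11.1%. This counts contacts and does not measure bias. The Protocol gives no effect size for the visits, so nothing here can be converted into FAC categories, steps or scale points.

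**Which assessments are exposed?** The visits come when the six weeks finish, and the first follow-up assessment comes directly after the intervention period. The visible text does not say whether the visits belong to that period.

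- If they do, the post-intervention FAC follows the visits and is exposed.
- If they do not, the FAC may come first and is then free of them.
- In either case the 6- and 12-month assessments follow the visits.

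Sites could also differ in the order, so that some primary scores follow a visit and others precede it.

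**Do content and outcomes overlap?** The visits teach use of gait gains in daily activities. Activity of daily living and participation are assessed at the end of intervention and at both later times. The overlap is direct for these outcomes and weaker for FAC.

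**The case against.** **The sentence may simply be misplaced.** The visitor is the physiotherapist engaged in conventional training, and both training arms have such training. The authors may have meant the visits for both. This stands as a possibility, but the text does not say it, and a site would act on the text.

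**The HAL arm may be meant as a programme.** Purpose and aims speaks of HAL as part of regular rehabilitation, and treadmill use and body weight support are fixed in that arm but optional in conventional training. A reader might infer that, without the visits, a difference could be attributed to HAL alone. The documents do not support that: these other differences would remain even with matched visits. The narrower point survives, because the stated contrast names training with and without HAL and does not mention home education.

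**Conventional training differs too.** Its ceiling is 18 × 30 minutes = 9 h in the HAL arm and 27 h in the first control group, and it may include "training of gait function in activities of daily living". A reader might infer a second imbalance, or a deliberate offset to the visits. Neither is supported. HAL walking replaces up to 60 of 90 minutes, so this is largely the treatment contrast itself; the figures are caps and not delivered doses; and the Protocol gives no offsetting rationale.

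**The timing may be settled elsewhere.** The assessment table is not shown. Also, since the visits stand under Interventions, it is natural to read them as preceding the assessment. Both remarks are fair. The first limits the claim to the visible text; the second, if right, means the primary FAC is exposed.

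**The stakes are limited.** The exposure is mainly in secondary outcomes, which the Protocol says it will explore. This stands, and it keeps the point modest.

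**Conclusion.** The point holds for the Protocol as written. One training arm is given 1 to 2 non-HAL home education visits per patient (54 to 108 in total) beyond a matched 90-minute session ceiling, and the other is given none. The HAL versus no-HAL contrast therefore includes a co-intervention at 6 and 12 months, mainly in daily-life outcomes. It includes it in the primary FAC only if the visits come before that assessment, which the visible text leaves open.

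This rests on two assumptions: that sites follow the text literally, and that the assessment table does not fix the order. The size and direction of any effect cannot be derived. It would be wrong to infer that the primary result is biased, or biased in favour of HAL: neither the order nor any effect of the visits is given. Sample size, significance level and power are untouched. The change is worth making because it is cheap and determines what the later comparisons can be said to show.

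**What to change.** In Interventions, state that the home visits take place after the post-intervention FAC assessment, so that the primary contrast is free of them. Describe the 6- and 12-month contrast as HAL training plus home visits versus intensive training without either. Because the visits would then fall in the 12-month utilisation window, state that study visits are not counted as health care use. This is a safeguard: nothing in the Protocol shows whether such visits would appear in the county council data.

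If the visits were meant for both training arms, one sentence saying so is enough and no relabelling is needed.

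If they were not, adding them to the first control group is optional. It would need 18 to 36 extra physiotherapist visits per site (54 to 108 overall), and the choice between a package contrast and a matched one is open to debate.

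The recommended change costs a few sentences and no extra visits. Its downsides are that the visits move to just after the six weeks, outside the primary outcome, and that the later contrast is described less favourably for HAL.

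### The protocol describes its adverse event outcome with two different scopes, and the treatment-related scope makes comparison with the no-intervention arm uninformative

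*Protocol*

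**What the plan says.** All of the relevant text is in the protocol under Methods and procedures.

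- **Study Endpoints**, among the secondary aims: "treatment related adverse events during the study will be documented".
- **Secondary outcome measures**: "Treatment related adverse events will be documented".
- **Power calculation and statistics**, in the paragraph on adverse events: "Adverse events during the study period adverse events (such as falls, skin impact, pain during training session with HAL; new stroke or other cardiovascular events". The same sentence goes on to say that these "will be documented according to a preformed protocol and their association or not to the Interventions will be classified by an external partner".
- **Interventions**: "The 2nd control group will not receive an intervention".

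Two further statements bear on what treatment means in that third arm. Study Endpoints calls it "c) standard training, in a later phase (1-10 years) after stroke". Data collection says that its participants "will document any scheduled training sessions in an web based application (app) or will be interviewed once a week".

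**The concern.** Two of the three statements on adverse events make relatedness to treatment part of the outcome itself. The third records events first and has relatedness assigned later by an outside party. A site or analyst could follow either, and the protocol does not say which prevails.

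The design makes this matter. One of the three arms receives no study intervention, and an event there can hardly be related to something that was not given. Falls, new strokes and cardiovascular events, which the protocol itself lists, can occur in any arm. Only a comparison of all events with the 2nd control group can show whether intensive training raises or lowers their frequency. The protocol has an interest in both directions. It asks about harm from training, and it presents cardiovascular function and secondary stroke prevention as possible benefits. A safety outcome limited to related events answers neither question against that arm.

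The reporting order could be settled in a later analysis plan. Events that were never recorded in one arm cannot be reliably recovered that way, so the scope of recording belongs in the protocol.

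**Working it through.** The protocol states no adverse event rate, so there is no figure to reproduce. The check is a comparison of the texts, followed by a labelled illustration.

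**Step 1: scope and order.**

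| Place in protocol | What is documented | When relatedness is decided |
|---|---|---|
| Study Endpoints | Treatment-related events | Not stated; it is part of the definition |
| Secondary outcome measures | Treatment-related events | Not stated; it is part of the definition |
| Power calculation and statistics | Adverse events in the study period, with examples that need not come from training | After documentation, by an external partner |

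The external partner classifies events as associated or not. The second option makes sense only if unrelated events are recorded too. The third row is therefore wider than the first two. All three places speak of events being documented; none draws a line between what is collected and what is reported.

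**Step 2: can the three be read together?** Yes. All events are recorded, the external partner classifies them, and the related ones form the declared outcome. Even so, the declared safety outcome is the related subset, and nothing commits the trial to comparing all events by arm.

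**Step 3: consequence for each contrast, taking treatment as the study intervention.**

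- HAL against conventional intensive training: both arms receive an intervention, so related events can arise in both and the contrast stays usable.
- Either training arm against the 2nd control group: the control count is structurally close to zero whatever the true risk, so the contrast is uninformative.

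**Step 4: size of the affected group.** The plan is for 18 patients per arm at each of 3 sites. That gives 18 × 3 = 54 per arm and 54 × 3 = 162 in all, so the 2nd control group is 54/162, one third of the trial.

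**Step 5: illustration with assumed values.** Let *p* be the true risk of an event, assumed equal in all arms, and *s* the share of events in a trained arm that are judged related. Expected patients with an event are 54 × *p* under all-event recording. Under a related-event outcome they are 54 × *p* × *s* in a trained arm and 0 in the 2nd control group.

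| *p* (assumed) | All events, each arm | Related, trained arm, *s* = 25% | *s* = 50% | *s* = 100% | Related, 2nd control group |
|---|---|---|---|---|---|
| 10% | 5.4 | 1.35 | 2.7 | 5.4 | 0 |
| 20% | 10.8 | 2.7 | 5.4 | 10.8 | 0 |
| 30% | 16.2 | 4.05 | 8.1 | 16.2 | 0 |

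Every row has equal true risk, yet the related-event columns show a difference of 1.35 to 16.2 patients. That difference reflects the definition and not the training.

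**The case against.** The strongest reply is that there is no true contradiction. Neither short statement says that related events alone are recorded. One is a clause in a list of aims and the other a sentence in a list of outcomes. The statistics section is the only place that describes a procedure, and it covers unrelated events. The texts can be reconciled, so no rule of precedence is needed. This reply largely stands: the statements are inconsistent in scope but do not exclude each other. It does not remove the point, because on the reconciled reading the declared outcome is still the related subset.

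A reader might draw three stronger conclusions that the protocol does not support.

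- *That unblinded site staff must judge relatedness before an event is recorded.* The protocol gives nobody at the sites that task. The only party with a role in relatedness is the external partner.
- *That safety cannot be compared at all.* HAL and conventional training can be compared under either scope. Only contrasts with the 2nd control group are affected.
- *That the 2nd control group can have no events by definition.* This holds only if treatment means the study intervention. The arm is elsewhere called standard training, and any scheduled sessions are logged, so on a looser meaning some events could count as treatment related.

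It is also fair to say that detailed questions and contact schedules belong in the case report form or in the preformed protocol for adverse events, neither of which is shown. Their absence is not criticised here. The definition of the population for safety data, which requires that the intervention program was started, raises a separate question about the same arm; this point does not rest on it.

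**Conclusion.** The point holds in a limited form. The protocol gives adverse events two scopes without saying which governs, and the one named as the outcome cannot inform comparisons with about 54 of 162 patients. The conclusion rests on reading treatment as the study intervention, and on the 2nd control group receiving none, as the Interventions section states. The numerical illustration is entirely assumed. It shows the direction of the distortion and a possible range, not its actual size in this trial. The defect is one of wording, and the sponsor's own statistics section already contains most of the remedy. It should still be corrected, because the correction is nearly free and unrecorded events cannot be restored afterwards.

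**What to change.** 1. In Study Endpoints and in Secondary outcome measures, replace treatment related adverse events with adverse events.
2. In the adverse event paragraph of the statistics section, state that documentation covers all three arms, over the same period and by the same method.
3. Keep the external partner's classification of relatedness as the step after documentation.
4. State that all events are reported by arm first, and the related subset second.

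The change is a few words in three places. Its cost is somewhat more event recording in the 2nd control group. That group already reports its training sessions through the app or a weekly interview, which could also be used to ask about events, provided the other arms are asked in the same way.
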